#### Follow-up

Clinical follow-up of the mother and neonate will be completed prior to hospital discharge.

#### Trial end

The trial will be considered complete after the final review of the last subject participating in the trial. Trial completion will be notified to the Competent Authority and the Ethics Committee using the appropriate form.

#### Statistical analysis

Data analysis and reporting will proceed according to CONSORT guidelines for randomised controlled trials, and will be conducted blinded to group status by the trial statistician and researcher. The first stage of analysis will be to use descriptive statistics to describe recruited individuals in relation to those eligible, and to investigate comparability of the trial arms at baseline. The primary analysis will involve an intention-to-treat comparison between the two groups for the primary outcome adjusted for stratification/minimisation factors – this will include study centre. Secondary outcomes will be analysed in a similar way. All analyses will use appropriate (that is, logistic or linear) regression models, with results presented as point estimates (odds ratios or difference in means), 95% confidence intervals and p values. Further secondary analyses will involve planned subgroup analyses and will use multivariable regression models with appropriate interaction terms to ascertain any differential effects in relation to, choice of instrument and operator experience.

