### The primary outcome is to compare the incidence of incorrect diagnosis of the fetal head position

The secondary outcomes are:

to compare the incidence of neonatal trauma, low Apgar scores, fetal acidosis or admission to the neonatal unit

to compare the incidence of primary postpartum haemorrhage, third and fourth degree perineal tears or prolonged postnatal admission

to compare the incidence of sequential use of instruments, instrumental delivery with more than one operator, failed instrumental delivery, transfer to theatre or caesarean section

to compare the decision-delivery intervals

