## Methods

### Recruitment and intervention

Recruitment of women to the study will follow a three stage process.

(1) All potentially eligible women will be given written information about the study in the antenatal clinic. A leaflet and covering letter will explain the trial purpose and design, making it clear that women will only become eligible for the study if they require an instrumental delivery. The leaflet will contain contact details to allow women to discuss the study further if they wish.

(2) Once a woman has presented in early labour or for induction of labour, a research fellow will seek written informed consent if the following criteria are satisfied:

i) the midwife looking after the woman assesses her to be capable of providing informed consent.

ii) the woman has adequate pain control.

iii) the woman has not used systemic opiates in the last four hours.

(3) Once consent has been given the mother will not be consulted again unless she requires an instrumental delivery. After confirmation that all criteria are met, the research midwife/fellow will obtain the allocation.

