#### Intervention arm

Women in the intervention group will be managed in the same way. In addition they will receive an ultrasound scan to assess the position of the fetal head and spine. Immediately before or after the clinical examination and before application of the instrument, the fetal head position will be determined sonographically by a trained research fellow. The research fellow will be trained before the start of the trial by a consultant sub-specialist in fetal and maternal medicine and perform a minimum of thirty five ultrasound assessments in the second stage of labour as described in the validation study [23]. For all ultrasound assessments, image- directed pulsed Doppler equipment (Sonosite Titan) with a multifrequency sector array transabdominal transducer, and a 3.5 MHz sector ultrasound probe, will be used.

With the patient in a supine position the ultrasound transducer will first be placed transversely over the maternal abdomen and moved longitudinally to identify landmarks for the fetal spine and head position as described in the validation study [23]. The transabdominal probe is then rotated through 90 degrees, to obtain the transverse view of the fetal spine. Following this, a sliding motion towards the fetal head will be made to obtain a view of the following midline fetal cranial structures: midline cerebral echo, falx cerebri and thalamus and anterior or posterior cranial structures including the orbits and nuchal region. The fetal head position will then be classified as previously described. The obstetrician will be informed of the ultrasound findings to facilitate decision making and may then proceed to instrumental delivery.

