#### Secondary outcomes

Secondary neonatal outcomes will include trauma, low Apgar scores, low arterial blood gases and admission to the neonatal intensive care unit (NICU). Neonatal trauma will include bruising, laceration, cephalhaematoma, retinal haemorrhage, facial nerve palsy, brachial plexus injury and fractures. Paired cord blood gases will be taken routinely to measure arterial and venous pH and base excess. Arterial pH below 7.10 and base excess greater than −12.0 mmol/l will be used as the threshold to define significant fetal acidosis.

Secondary maternal outcomes will include extensive perineal tearing involving the anal sphincter (third or fourth degree tears), postpartum haemorrhage, shoulder dystocia, and length of postnatal hospital stay. Primary post partum haemorrhage is defined as an estimated blood loss at delivery and in the first 24 hours of more than 500mls. Postnatal stay will be considered prolonged if more than 3 days’ duration. Maternal and neonatal complications will be defined clinically according to the attending clinicians.

Procedural issues will be recorded in terms of place of delivery, need for senior obstetric support, transfer to theatre, use of sequential instruments, failure of instrumental delivery or proceeding directly to caesarean section and the decision to delivery interval.

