## Discussion

### Potential and implementation of the findings

It is both important and timely to evaluate the use of ultrasound to diagnose the fetal head position prior to instrumental delivery. To date most studies relating to the use ultrasound for diagnosis the fetal head position have been observational studies with only one small randomised controlled trial found and although the results are promising, this use of ultrasound needs to be formally evaluated within the setting of a clinical trial before its routine use can be advocated.

Misdiagnosis of the fetal head position at digital vaginal examination is more likely with the clinically important malpositions, especially OP, leading to attempts to deliver vaginally with incorrectly applied instruments. Furthermore, uncertainty about the fetal head position may be a factor in the decision to transfer more women to theatre for a trial of instrument, causing in some cases an unnecessary delay in delivery and wasting valuable theatre time; equally failed instrumental delivery in a labour room due to incorrect diagnosis of the fetal head position is associated with increased physical and psychological morbidity. Accurately diagnosing a malposition of the fetal head prior to instrumental delivery may lead to appropriate use of senior support, transfer to theatre for trial of instruments or indeed abandoning the procedure in favour of a caesarean section. The overall aim is to reduce the incidence of incorrect diagnosis of the fetal head position prior to instrumental delivery and improve the safety of instrumental deliveries.

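### Both planned subgroup interactions, on choice of instrument and operator experience, use variables that the scan can change because neither is tied to its pre-allocation value

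*Protocol article*

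**What the plan says.** Under Statistical analysis, the protocol plans secondary analyses that will "use multivariable regression models with appropriate interaction terms to ascertain any differential effects in relation to, choice of instrument and operator experience". These are the only subgroup variables named, and the text does not say when either is measured or whose experience counts.

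The order of events is given elsewhere:

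- **Allocation** (Recruitment and intervention): once a woman needs an instrumental delivery, "After confirmation that all criteria are met, the research midwife/fellow will obtain the allocation".
- **Scan** (Intervention arm): "before application of the instrument, the fetal head position will be determined sonographically by a trained research fellow".
- **Use of the result** (Intervention arm): "The obstetrician will be informed of the ultrasound findings to facilitate decision making and may then proceed to instrumental delivery".

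The Discussion states an expected consequence: "Accurately diagnosing a malposition of the fetal head prior to instrumental delivery may lead to appropriate use of senior support". It adds transfer to theatre and abandonment in favour of caesarean section as further possibilities.

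Related measures are listed as outcomes. The secondary objectives include an aim "to compare the incidence of sequential use of instruments, instrumental delivery with more than one operator, failed instrumental delivery". The Secondary outcomes section records "place of delivery, need for senior obstetric support, transfer to theatre, use of sequential instruments". Randomisation is stratified by centre only (Allocation to trial groups).

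**The concern.** A treatment-by-subgroup interaction can be read as effect modification when subgroup membership is unaffected by treatment. If the scan changes who is delivered with which instrument, or by whom, and does so according to head position, then women in the same subgroup of the two arms are not comparable. Head position also predicts the outcome: the Literature review reports that digital errors are more likely in occipito-posterior positions. An interaction can then appear when the scan works equally well in everyone, or be hidden when it does not.

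The results would be read as showing with which instrument, and in whose hands, ultrasound helps. Part of that answer could come from selection after randomisation.

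**Working it through.** **Setting the passages side by side.** The sequence in the intervention arm is allocation, scan, obstetrician informed, instrument applied. Whatever is decided after the third step can depend on the arm.

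- *Operator experience:* the Discussion itself expects accurate diagnosis to alter senior support, and operator measures are listed as outcomes. If the variable means the delivering operator, the protocol supports the problem directly.
- *Choice of instrument:* no sentence says that the scan changes the instrument. The link is inferred from the obstetrician learning the position before application, for the stated purpose of helping decisions.

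**The plan's own figure.** The protocol gives no figure for the interaction tests, so I checked the sample size whose inputs I use: 20% versus 10%, two-sided 5%, 80% power.

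n = [1.96 × √(2 × 0.15 × 0.85) + 0.8416 × √(0.16 + 0.09)]² / 0.10² = 199 per arm. With continuity correction, n = (199/4) × [1 + √(1 + 4/(199 × 0.10))]² = 219. The stated 225 is within 3% of this.

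**Scenario 1 (assumed inputs except the 20% and 10%).** Assume 40% malposition. All errors are malpositions called occipito-anterior (OA). Instrument A is used in 90% of believed malpositions and in 20% of the rest. The scan halves the error risk uniformly. Per 100 women per arm:

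- Usual care: 20 believed malposition, 80 believed OA. A has 0.9 × 20 + 0.2 × 80 = 34 women with 0.2 × 20 = 4 errors. B has 66 women with 16 errors.
- Intervention: 30 believed malposition, 70 believed OA. A has 0.9 × 30 + 0.2 × 70 = 41 women with 0.2 × 10 = 2 errors. B has 59 women with 8 errors.

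The RR in A is (2/41)/(4/34) = 0.41, and in B (8/59)/(16/66) = 0.56. The OR in A is (2/39)/(4/30) = 0.38, and in B (8/51)/(16/50) = 0.49. The ratio of ORs is 0.78.

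At 225 per arm every count is multiplied by 2.25, so A has 9 versus 4.5 expected events and B 36 versus 18. SE of the log ratio = √(sum of 1/cell over eight cells) = 0.68. z = |ln 0.785|/0.68 = 0.36. Rejection probability = 1 − Φ(1.96 − 0.36) + Φ(−1.96 − 0.36) = 6.5%, against 5%.

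One limit: this scenario holds the RR constant, so the ratio of ORs would not be exactly 1 without the shift. Halving the usual-care stratum risks gives ORs of 0.47 and 0.43, a ratio of 1.09.

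**Scenario 2 (assumed inputs except n and the approximate rates).** Assume 30% hard positions, usual-care error 10% in easy and 43.3% in hard positions (20% overall), and a true OR of 0.42 in both types. Intervention risks are then 4.5% and 24.3% (10.4% overall). Subgroup A is one instrument, or senior operators. Each cell risk is the mix of hard and easy women in it, and the same Wald test is used.

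| Share in A, usual care (hard/easy) | Share in A, scan arm (hard/easy) | OR in A | OR in B | Ratio | Rejection |
|---|---|---|---|---|---|
| 40%/40% | 40%/40% | 0.46 | 0.46 | 1.00 | 5% |
| 40%/40% | 55%/35% | 0.57 | 0.40 | 1.44 | 10% |
| 40%/40% | 70%/30% | 0.67 | 0.33 | 2.06 | 25% |
| 40%/40% | 80%/20% | 0.82 | 0.27 | 3.00 | 50% |
| 60%/32% | 70%/30% | 0.51 | 0.41 | 1.25 | 7% |
| 70%/25% | 80%/20% | 0.52 | 0.39 | 1.34 | 8% |
| 55%/35% | 70%/30% | 0.55 | 0.38 | 1.44 | 10% |

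With no effect of the scan on error at all (OR 1.00), the shifts in rows 2 to 4 give rejection of 12%, 32% and 61%. With membership equal in both arms, as a pre-allocation variable ensures apart from chance, rejection is 5%. That holds even when membership depends on position: 70%/30% in both arms gives a ratio of 1.01.

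The ratio is below 1 in Scenario 1 and above 1 in Scenario 2, so the direction cannot be predicted.

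**The case against.** A reader might infer that these tests are bound to produce false subgroup findings and that the plan cannot stand without change. The documents do not support that, for five reasons.

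- **Size.** In Scenario 1 the test is almost undisturbed: 1.5 percentage points above nominal, with benefit in the same direction in both strata. The 25% and 50% rows assume that usual-care membership ignores head position. Usual-care obstetricians also assess position before proceeding (Usual care arm). Once membership depends on position in both arms, the rows shown fall to 7% to 10%. No shift, large or small, is given in the protocol.
- **Instrument.** That the scan changes the instrument is inference, as noted above.
- **Operator.** Calling for senior support is not the same variable as the experience of the obstetrician who decided on the delivery. If the latter is meant, and it is fixed before allocation, that interaction is sound.
- **Caesarean section.** A reader might also infer that women who go straight to caesarean drop out of the instrument analysis. They may have no instrument to classify, but the protocol states no such exclusion and gives no basis for sizing it.
- **Detail left elsewhere.** A journal article may leave the definitions to the full protocol or the statistical analysis plan.

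The first four points stand and limit the claim. The last stands only in part. The article does fix the two variables, and the ordinary reading of choice of instrument is the choice made when the instrument is used. A later analysis plan also cannot recover a pre-allocation value that was not recorded, and nothing in the article says that either is.

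**Conclusion.** The point holds in a limited form. As written, both planned interactions can condition on consequences of the intervention. The text supports this directly if operator experience means the delivering operator, and by inference for the instrument. Bias arises only if the scan moves women between subgroups according to head position or difficulty. Its direction is open and its size cannot be taken from the documents. Under the assumptions shown, rejection of a true null interaction ranges from about 6.5% to 50% against 5%, and the upper end needs one-sided assumptions.

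The primary intention-to-treat comparison and the sample size are not affected. This should be fixed, as a defect in a secondary analysis; it does not threaten the trial's main conclusion.

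**What to change.** - Define the operator subgroup as the grade of the obstetrician who made the decision for instrumental delivery, recorded before the allocation is released.
- Keep instrument as a subgroup only if the intended instrument is recorded before allocation. Otherwise drop that interaction.
- Report the instrument actually used and the delivering operator's experience by arm as process outcomes, with no claim of effect modification.

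The cost is one or two fields before the web allocation and a sentence in the analysis section. The operator field is simple. The intended instrument is less so: the protocol describes the documented clinical examination as part of care after allocation, so an intention named earlier may be a weak proxy for the real choice. It also adds a step in a setting that the Feasibility section describes as pressured. If that is not worth it, dropping the instrument interaction costs nothing. For women already randomised without these fields, the values cannot be reliably reconstructed.

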#### Feasibility

We have completed a prospective cohort study and multi-centre randomised controlled trial comparing restrictive versus routine use of episiotomy at instrumental delivery [24,25]. Interventional studies in the second stage of labour require great sensitivity in terms of appropriate recruitment, randomisation and follow-up. A large number of women need to be approached in the antenatal period of whom only a small proportion will ultimately be invited to participate in the trial. The number of women who are eligible but not recruited needs to be recorded. Obstetricians and midwives are under pressure when planning instrumental delivery in the second stage of labour which needs to be taken in to consideration when designing a second stage clinical trial. Our research team has extensive experience of performing studies in this context and the proposed study design and sample size reflects an accurate estimate of what is feasible within the proposed time frame and available resources.

#### Sample size

The rate of inaccurate diagnosis (difference of more than 45 degrees) was hypothesized to be 20% in the usual care arm (clinical assessment alone) and 10% in the intervention arm (clinical assessment and ultrasound). With 225 women per arm, the study will have 80% power with 5% two-sided alpha, to detect the hypothesized 10% difference. However, it is possible that inaccuracy rates are being under- or over- estimated. It could be argued that any difference in effect on the primary clinical outcome would be worth detecting. Rather, given the need for timely delivery of evidence, we have specified detectable differences for realistic sample sizes recruited within a reasonable time frame within the constraints of the available funding.

The combined annual birth rate for the two recruiting hospitals is 13,500, and around 40% of women will be nulliparous, of whom 30% will have an instrumental delivery. We estimate that there will be a total of 3240 instrumental deliveries among nulliparous women over the 24 month recruitment period based on hospital statistics for 2007. Allowing for 30-50% exclusion and non-consent, 95% collection of the primary outcome, and recruiting for 24 months during office hours yields a conservative estimate of 450 participants (225 per arm) for analysis. This would enable detection of a between-group difference of 10–13 percentage points (odds ratio 0.44 to 0.55) with 80% power and 5% two-sided alpha, and would certainly be considered by women and clinicians as worthwhile. These conservative recruitment estimates take account of eligibility criteria, non-english speaking women and the potential difficulty of randomisation and ultrasound evaluation in the context of suspected “fetal distress”.

#### Timetable

Total 36 months: Commencing 01.12.10 - Estimated completion date 31.12.13

1–6 months: regulatory approvals, pre-trial ultrasound training and pilot study

7–31 months, recruitment, intervention, data collection

32–36 months, data analysis/reporting; Peer-review publications; Presentations.

### Governance issues

#### Ethical committee permission

Ethical committee approval from the Coombe Women & Infants University Hospital and the Mid-Western Regional Maternity Hospital, Limerick, have been granted for this study.

#### Data management

Data will be collected on a case report form (CRF) at the time of recruitment by a trained researcher. The researcher will also be responsible for ensuring that the details of the delivery are recorded and documented according to the study protocol. The inpatient maternal and neonatal notes will be marked so that they can easily be recovered following discharge from hospital. After discharge the CRF will be collected by the local co-ordinator and the completeness of the data checked against the woman’s and neonate’s notes. Any errors will be followed up at this time. The data will be entered into a computer database (password protected) at the Coombe Women and Infants University Hospital.

#### Trial management group (TMG)

This group will be in charge of the everyday running of the trial. The full group will meet 4-monthly and as required. Day-to-day decision making will be by [name], [name] and the trial researcher, with meeting of the full committee as above.

#### Trial steering committee

A trial steering committee will be set up which will have overall supervision of the trial. It will meet prior to commencement of the trial and then at least 6 monthly until completion. A meeting of the TSC will be held within a month of every DMEC meeting to consider their recommendations. An independent Chair will be sought for the TSC.

#### Data monitoring and ethics committee (DMEC)

An independent safety and data monitoring committee will also be formed. They will meet 6-monthly. They will advise the Trial Steering Committee (TSC) on the need for continuing or stopping the trial.

#### Safety considerations

Serious adverse events (SAEs) will be recorded and reported to the regulatory authorities. SAEs include maternal death, surgery (other than caesarean section) admission to intensive care unit or perinatal death. In the event of a SAE occurring, a form will be completed by the local researcher and faxed to the trial co-ordinating centre at the Coombe Women’s Hospital within 72 hours. The chair of the Data Monitoring and Ethics Committee (DMEC) will be informed and the Chair of the MREC will also be informed by the DMEC Chair if considered appropriate.

## Discussion

### Potential and implementation of the findings

It is both important and timely to evaluate the use of ultrasound to diagnose the fetal head position prior to instrumental delivery. To date most studies relating to the use ultrasound for diagnosis the fetal head position have been observational studies with only one small randomised controlled trial found and although the results are promising, this use of ultrasound needs to be formally evaluated within the setting of a clinical trial before its routine use can be advocated.

Misdiagnosis of the fetal head position at digital vaginal examination is more likely with the clinically important malpositions, especially OP, leading to attempts to deliver vaginally with incorrectly applied instruments. Furthermore, uncertainty about the fetal head position may be a factor in the decision to transfer more women to theatre for a trial of instrument, causing in some cases an unnecessary delay in delivery and wasting valuable theatre time; equally failed instrumental delivery in a labour room due to incorrect diagnosis of the fetal head position is associated with increased physical and psychological morbidity. Accurately diagnosing a malposition of the fetal head prior to instrumental delivery may lead to appropriate use of senior support, transfer to theatre for trial of instruments or indeed abandoning the procedure in favour of a caesarean section. The overall aim is to reduce the incidence of incorrect diagnosis of the fetal head position prior to instrumental delivery and improve the safety of instrumental deliveries.

